#### Costs

Direct intervention costs will be recorded prospectively. Healthcare resource use will include trial-intervention resource use (e.g., CVR clinician’s time) and non-trial healthcare use which may be impacted (e.g., hospital visits, where patients have consented to medical record access), costed using actual costs accrued where available or market rate estimates.

### Sample size

The sample size calculation for the 2-arm randomised control trial is based on an increase in 6MWT-distance as a result of aerobic exercise programs similar in design to cardiac rehabilitation exercise programs for survivors of stroke [58]. This systematic review and meta-analysis found an effect size of 0.41 (Hedges’ g corrected effect size) for 6MWT-distance. With a Cohen’s f = 0.205 (half Hedges’ g), three repeated measures (baseline, 6-weeks, and 6-months), a two-sided significance test at a 5% alpha level, a power of 80%, and assuming 0.5 as the correlation among repeated measures, the total sample size required is 128 (64 per arm), calculated using G*Power version 3.1.9.4. Assuming an 8% drop-out rate as commonly found in stroke research [59], the final sample size is 140, with 70 in each group.

### Data analyses

All participants who complete the baseline assessment and attend at least one CVR session will be included in the analysis. Descriptive statistics will be completed, and feasibility measures will be reported as percentages. Data will be analysed according to group assignment for participants with TIA or mild stroke following intention-to-treat principles. To analyse 6MWT-distance and all other secondary outcomes, methods for repeated measures analysis will be used. Linear (for continuous outcome data) and Generalised Linear (for Binary and Count outcome data) mixed-effects models for repeated measures will be used for between-within group comparisons and time-interactions analyses adjusting for demographic characteristics and other potential covariates, such as time since TIA or mild stroke. All analyses will be conducted using either SPSS or STATA. Any estimate will be reported with associated 95% confidence intervals. Significance level will be set at p < 0.05.

Implementation outcomes will be evaluated using both quantitative and qualitative methods. The Reach, Effectiveness, Adoption, Implementation, Maintenance (RE-AIM).

framework will be used to assess implementation outcomes such as characteristics of participants (reach), change in 6-min walk distance (effectiveness), number of referrers and characteristics of CVR program clinicians (adoption), fidelity and cost of the intervention (implementation) and drop-out rates (maintenance) [60]. A qualitative thematic analysis of semi-structured interviews from both participants and health professionals involved in the CVR program will also be undertaken. Two research team members will independently code and identify potential themes using an inductive thematic approach [61]. Emerging themes will be discussed until consensus is reached on final themes and categories. Deductive analyses will be mapped to the Consolidated Framework for Implementation Research (CFIR) [62] constructs to understand how the CVR program works and factors that influence implementation success or failure. The Intervention Characteristics and Inner Settings domains will be primarily considered as they are more relevant for this type 1 effectiveness-implementation hybrid trial.

The effect of the intervention on the rates of unplanned CVD-related hospital admissions and emergency department visits within the 6-months study period using a cost-effectiveness analysis will also be evaluated. Information on secondary measures such as health behaviour change (moderate-to-vigorous physical activity), BMI, waist circumference, quality of life (AQoL-6D), clinical and demographic information and the costs associated with the use and delivery of the CVR program will be used. A cost-utility analysis will be undertaken with a societal perspective using gained quality-adjusted life years (QALYs) as the measure of health effects. The impact on health-related quality of life can be measured using the AQoL-6D and the incremental cost-effectiveness ratios (ICERs) per QALYs will be calculated [63]. Information on the participants’ health service utilisation costs, based on the AR-DRG and URG classification codes will also be used. From these analyses, the additional cost per unit of health benefit gained over the lifetime (by using the CVR program compared to usual care) can be determined.

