## Methods

### Design

The type 1 effectiveness-implementation hybrid study [36] will use a 2-arm single-centre assessor-blind randomised controlled trial design and will be conducted in Canberra, Australia, commencing in 2022 (Fig. 1). People with TIA and mild stroke will be randomised to a 6-week exercise-based Cardiovascular Rehabilitation (CVR) program or a usual care 6-month wait-list control group. Recruitment will be staggered over 18-months and the total study duration for each participant will be 6-months from commencing the study.

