### Randomisation

An investigator not involved in recruitment or assessments will use a computer-generated random number sequence, with participants allocated in a 1:1 ratio. Group allocation will be concealed using sealed, consecutively numbered opaque envelopes. Following each participant’s baseline assessment, the next envelope in the sequence will be opened to reveal random allocation to one of two groups: the Cardiovascular Rehabilitation program or the 6-month wait-list control group.

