### Usual care control group

Those randomised to the control group will participate in usual care following a TIA or mild stroke. In Australia, this typically consists of follow-up with a neurologist and little or no secondary prevention other than pharmacological management [42]. Control participants will be wait-listed for the CVR program and will commence the CVR program 6-months after they have completed their baseline measures.

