### Outcome measures

All outcome measures will be collected at baseline, 6-weeks, and 6-months. Assessor blinding to group allocation will be used throughout the study. Research assistants will collect all outcome measures following training, using a standardised protocol and the same research grade equipment.

The primary outcome measure will be distance completed in the 6-min walk test and reported as metres (functional exercise capacity). Secondary outcome measures include daily minutes of accelerometer moderate-to-vigorous physical activity, body mass index, waist circumference, blood pressure, quality of life (AQoL-6D), anxiety and depression (HADS) and unplanned cardiovascular disease-related emergency department and hospital admissions. Qualitative data will be collected from participants and health professionals at the end of the intervention period, and cost analyses will be conducted. Demographic and clinical information will be collected using a questionnaire, including questions on sociodemographic variables (e.g., gender, age, education level) as well as clinical predictor variables (e.g., stroke-related medication, other medical conditions, smoking status). The research assistants will also record participant admission diagnosis and date of event or intervention details.

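### The analysis set requires attendance at a CVR session after randomisation, which contradicts the intention-to-treat claim in the same paragraph and cannot be applied to controls by the final assessment

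*Protocol article*

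**What the plan says.** The Data analyses section of the protocol article opens by fixing who is analysed: "All participants who complete the baseline assessment and attend at least one CVR session will be included in the analysis". The sentence names no arm. The next sentence concerns descriptive and feasibility reporting. The third reads: "Data will be analysed according to group assignment for participants with TIA or mild stroke following intention-to-treat principles".

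The timing comes from four other sections:

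- Randomisation: "Following each participant’s baseline assessment, the next envelope in the sequence will be opened to reveal random allocation to one of two groups".
- Outcome measures: "All outcome measures will be collected at baseline, 6-weeks, and 6-months".
- Design: "the total study duration for each participant will be 6-months from commencing the study".
- Usual care control group: "Control participants will be wait-listed for the CVR program and will commence the CVR program 6-months after they have completed their baseline measures".

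Nothing in the article limits the attendance condition to the CVR arm or labels the set modified intention-to-treat.

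**The concern.** Allocation is revealed after the baseline assessment, so attending a session is a post-randomisation event. Selecting participants on it is not intention-to-treat, whichever arm it is applied to.

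The rule governs the 6-minute walk comparison, and presumably every secondary outcome. As worded it cannot be applied to controls within follow-up. If it is applied to the CVR arm alone, it removes one kind of participant from one side only. The effect estimate would then describe people who start the programme, whereas the research question compares the programme with usual care. The cost-utility result would have the same limit if it uses the same set. Two incompatible definitions also leave the primary population open to choice after the data are seen.

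**Working it through.** **1. Can a control meet the condition?** The last outcome assessment is at 6 months, and each participant's study duration is 6 months. A control "will commence the CVR program 6-months after they have completed their baseline measures". By the final assessment, therefore, no control following the protocol has attended a session, yet the sample size counts 64 analysed controls. Counting attendance after that visit would make inclusion depend on an event later than the outcome.

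**2. The plan's own sample size.** Inputs from the Sample size section: f = 0.205 (half of g = 0.41), m = 3 measures, correlation ρ = 0.5, two-sided 5% alpha, 80% power. The G*Power between-factors formula has noncentrality λ = f²·N·m / (1 + (m − 1)ρ).

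- N = 128: λ = 0.205² × 128 × 3 / 2 = 8.07 on 1 and 126 df, power 80.5%.
- N = 126: power 79.9%. So 128 is the smallest even total, as stated.
- Drop-out: 128 / 0.92 = 139.1, which becomes 140, as stated.

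**3. Shift if CVR non-attenders are dropped.** Let q be the proportion of the CVR arm who never attend and s the SD by which they would walk less than attenders. The full-arm mean is the attenders' mean minus q·s, so dropping non-attenders raises it by q·s. The documents give neither quantity. I assume q = 0.10–0.20 and s = 0.3–0.5.

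| Analysis | Low (q = 0.10, s = 0.3) | High (q = 0.20, s = 0.5) | Share of 0.41 |
|---|---|---|---|
| No baseline adjustment, q·s | 0.03 SD | 0.10 SD | 7–24% |
| Baseline-adjusted, q·s·(1 − 0.5) | 0.015 SD | 0.05 SD | 4–12% |
| Change from baseline, stable deficit, q·(s − s) | 0 | 0 | 0% |

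The second row assumes the same deficit and SD at baseline as at follow-up, and uses the protocol's correlation of 0.5. With no true effect and no baseline adjustment, two-sided rejection rises from 5% to about 5.5% (low) and 9.9% (high).

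**4. Power after exclusion, effect held at 0.41.** With unequal arms, λ = 0.41² × [n₁n₂ / (n₁ + n₂)] × 1.5. Equal arms of 64 return 8.07 and 80.5%.

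| Non-starters | CVR v control | Power |
|---|---|---|
| 10%, in addition to drop-out | 57.6 v 64 | 78.3% |
| 20%, in addition to drop-out | 51.2 v 64 | 75.7% |
| 10%, taken from 70 | 63 v 64 | 80.2% |
| 20%, taken from 70 | 56 v 64 | 77.7% |

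The largest loss is 80.5 − 75.7 = 4.8 points.

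**The case against.** Four points on the other side deserve weight.

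- **An empty control arm.** A reader might infer that the sentence excludes every control and leaves none to analyse. The text does not go that far. The sentence sets no time limit, a control who later attends meets its words, and 64 per arm with between-group comparisons is clearly planned. What stands is narrower: the condition cannot be met by the final assessment, and waiting for later attendance would select on an event after the outcome.
- **Hidden uptake.** A reader might also infer that poor uptake would go unseen. The Feasibility section records sessions attended, dropouts and losses to follow-up, and Data analyses reports feasibility as percentages. Uptake would be reported. Only its effect on the estimate would be lost.
- **The drop-out allowance.** It is tempting to say that the 8% leaves out non-starters. The Sample size section does not define drop-out, so this is undetermined. Either way the power loss is small and does not carry the argument.
- **Size and direction of bias.** The planned mixed models include time interactions and covariates, and the walk test is measured at baseline, so the unadjusted range is an upper one. That non-attenders would do worse is plausible but not documented.

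The opening sentence could also be read as covering only descriptive and feasibility reporting. That is strained, because it refers to the analysis without qualification. None of these points reconciles the attendance condition with intention-to-treat.

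**Conclusion.** The point holds as a contradiction in the stated text, so it does not depend on what an unseen analysis plan may contain. The attendance condition conflicts with the intention-to-treat statement. It either cannot be applied to controls by the final assessment or, on the likely reading, excludes non-starters from the CVR arm only.

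The resulting bias plausibly favours CVR. Under the assumed 10–20% non-attendance and 0.3–0.5 SD deficit, it lies between about zero and 24% of the planned effect, depending mainly on how baseline is used. Bias that survives baseline adjustment would come from differences in later course, on which the documents give nothing. The sample size itself is correctly derived. The sentence needs correcting before analysis, because it defines the population for the primary comparison.

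**What to change.** Replace the opening sentence of Data analyses with: *All randomised participants with TIA or mild stroke will be analysed in the group to which they were allocated, regardless of CVR attendance, using all available outcome data.* State that 6-week and 6-month outcome visits continue for CVR participants who never attend. Present any attendance-based set only as a labelled supplementary analysis, and say which set the cost-utility analysis uses.

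The cost is one sentence plus follow-up of non-attenders. The planned 128 evaluable and 140 randomised stand. The estimated effect may be somewhat smaller. For illustration, if 0.41 applied to attenders only and non-attenders gained nothing, the all-randomised effect at 10% non-attendance would be 0.41 × 0.90 = 0.369 (power 71.8% at 64 v 64), and at 20% it would be 0.41 × 0.80 = 0.328 (61.6%). The article does not say whether 0.41 is an effect in attenders or in all allocated. Any such dilution reflects uptake and is part of the comparison with usual care that the trial sets out to make.

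### The analysis section does not adjust for the baseline value or set a common baseline mean; under the usual group-by-time model this costs precision, not validity

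*Protocol article*

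**What the plan says.** All places are in the protocol article.

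- **Outcome measures:** "The primary outcome measure will be distance completed in the 6-min walk test and reported as metres". On timing: "All outcome measures will be collected at baseline, 6-weeks, and 6-months".
- **Sample size:** the calculation uses "three repeated measures (baseline, 6-weeks, and 6-months), a two-sided significance test at a 5% alpha level", with 80% power, Cohen's f of 0.205 (half of a Hedges' g of 0.41) and a correlation of 0.5 among the repeated measures. It gives 128 in total (64 per arm), raised to 140 for 8% drop-out.
- **Data analyses:** "To analyse 6MWT-distance and all other secondary outcomes, methods for repeated measures analysis will be used". Continuous outcomes get linear mixed-effects models, used for comparisons between and within groups and for time interactions, "adjusting for demographic characteristics and other potential covariates, such as time since TIA or mild stroke".
- **Randomisation:** the allocation envelope is opened after the baseline assessment.

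Nowhere does the article name the baseline value of an outcome as a covariate, say that the arms share a baseline mean, or say which contrast from the model is the treatment effect.

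**The concern.** Read together, the Sample size and Data analyses sections most naturally describe a model in which baseline is one of three responses, with group, time and their interaction, plus fixed participant characteristics. In its usual form that model estimates a separate baseline mean for each arm.

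Two consequences follow. The group-by-time contrast at a follow-up visit then subtracts the whole baseline difference (a slope of 1) instead of the fraction that the correlation supports. Any group main effect averages in a visit made before randomisation, where there is no treatment effect to find.

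The baseline value is already collected for the walk test and for every other continuous outcome: accelerometer activity, body mass index, waist circumference, blood pressure, AQoL-6D and HADS. At stake is precision that could be had without more participants or visits.

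**Working it through.** **Inputs.** From the Sample size section: standardised effect d = 0.41, f = 0.205, m = 3 measures, correlation ρ = 0.5, two-sided α = 0.05, n = 64 per arm. Correlations other than 0.5 are assumptions, because the article gives no observed value for the walk test. Variances are in units of the outcome variance, taken as equal at all visits with equal correlations and complete data.

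**1. Reproduce the protocol's figure.** For the between-group test in a repeated-measures ANOVA, λ = f²·N·m / (1 + (m − 1)ρ).
- N = 128: λ = 0.205² × 128 × 3 / 2 = 8.07 on 1 and 126 df, power 0.805. At N = 126 the power is 0.799. So 128 reproduces.
- Drop-out: 128 / 0.92 = 139.1, which gives 140.
- The interaction version, λ = f²·N·m / (1 − ρ), reaches 80% at N = 40 and does not give 128.

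The stated size therefore belongs to a group effect averaged over all three visits, baseline included.

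**2. Variance of a single-visit contrast, per arm.**
- Change score: 2(1 − ρ).
- Baseline-adjusted: 1 − ρ².
- Ratio, adjusted to change: (1 + ρ)/2.

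**3. Check that the free-means model is the change score.** The generalised least squares variance of the 6-month group-by-time coefficient, 64 per arm, ρ = 0.5:
- Baseline means free: 0.03125. Change score: (2/64) × 1.00 = 0.03125.
- Baseline means constrained equal: 0.02344. Baseline-adjusted: (2/64) × 0.75 = 0.02344.

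Each pair agrees. Fixed covariates entered as main effects shift all three visits of a participant by the same amount, so they cancel from the change.

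**4. Size.** Power from the noncentral F with 1 and 126 df, λ = n·d² / (2 × variance). At ρ = 0.5: 64 × 0.1681 / 2 = 5.38 for the change score, and 5.38 / 0.75 = 7.17 after adjustment.

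| ρ | Change score | Adjusted | Variance saved | Power, change | Power, adjusted |
|---|---|---|---|---|---|
| 0.3 | 1.40 | 0.91 | 35% | 49% | 67% |
| 0.5 | 1.00 | 0.75 | 25% | 63% | 76% |
| 0.7 | 0.60 | 0.51 | 15% | 84% | 90% |
| 0.8 | 0.40 | 0.36 | 10% | 95% | 97% |
| 0.9 | 0.20 | 0.19 | 5% | above 99% | above 99% |

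For the mean of the two follow-ups at ρ = 0.5, the variances are 0.75 (change) and 0.50 (adjusted), and power is 76% and 90%.

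**5. Dilution of a three-visit group effect.** If the effect is 0.41 at both follow-ups and zero at baseline, the average over three visits is 0.41 × 2/3 = 0.273. The variance of the three-visit mean is (1 + 2 × 0.5)/3 = 0.667. Then λ = 64 × 0.273² / (2 × 0.667) = 3.59 and power is about 47%.

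**The case against.** **The article does not fix the model.** Only the Sample size section counts baseline as a repeated measure. Data analyses does not say that baseline is in the response or that the arms' baseline means are left free, and the words before time since the event mark it as an example. A reader might infer that the protocol rules out baseline adjustment and commits to a change-score analysis. The text does not support that. This stands and limits the point to a conditional one. The open list is only a partial answer, however: if baseline is already a response, adding it as a main-effect covariate puts it on both sides of one model and is not the adjustment meant here.

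**Baseline as a response is not the fault.** A model that keeps baseline in the response with a common mean for the arms loses nothing. This stands. What is missing is either that constraint or a baseline covariate.

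**A condensed article may leave this to the analysis plan.** That holds for covariance structure and the final covariate list, and nothing is asked about those. But the article does give a model class, a role for baseline, a type of contrast and the kind of adjuster, and together these point to a less efficient analysis than the data allow.

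**Nothing is invalid.** A reader might infer bias or an inflated type I error. Neither follows: under randomisation the change-score contrast is unbiased, and it does account for chance baseline differences, only less efficiently.

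**The gain may be small.** At ρ = 0.8 or above it is slight. This stands, although 0.5 is the protocol's own planning value.

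**Conclusion.** The point holds as a costless gain in precision. On the natural reading of the two sections, and if the arms' baseline means are left free, the follow-up contrast is a change-score difference. Adjusting for baseline would then lower its variance by 25% at ρ = 0.5, 10% at ρ = 0.8 and 5% at ρ = 0.9. At d = 0.41 and 64 per arm, single-visit power goes from 63% to 76% at ρ = 0.5, and from 95% to 97% at ρ = 0.8.

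These figures assume equal variances and correlations across visits, complete data and a single-visit contrast, which the article does not designate as primary. The 47% for a three-visit group effect further assumes that the full effect is present at both follow-ups.

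It would be too strong to conclude that the trial is underpowered. The true correlation is not given, and at 0.7 or above even the change score exceeds 80% for a single visit.

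**What to change.** In Data analyses, for each continuous outcome, state one of two equivalent models:

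- model the 6-week and 6-month values with group, visit, group-by-visit, that outcome's baseline value and baseline-by-visit; or
- keep baseline in the response with the arms' baseline means constrained equal.

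State also that the treatment effect is the post-baseline contrast between arms, not a group effect averaged over all three visits. The covariates already planned can stay.

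The cost is a few sentences in the analysis text. Participants, visits, data and the planned software (SPSS or Stata) are unchanged.

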**Methods:**

This type 1 effectiveness-implementation hybrid study will use a 2-arm single-centre assessor-blind randomised controlled trial design, recruiting 140 participants. Adults who have had a TIA or mild stroke in the last 12-months will be recruited by health professionals from hospital and primary healthcare services. Participants will be assessed and randomly allocated (1:1) to the 6-week CVR program or the usual care 6-month wait-list control group. Distance completed in the 6-min walk test will be the primary effectiveness outcome, with outcomes collected at baseline, 6-weeks (complete CVR) and 6-months in both groups. Other effectiveness outcome measures include unplanned cardiovascular disease-related emergency department and hospital admissions, daily minutes of accelerometer moderate-to-vigorous physical activity, body mass index, waist circumference, blood pressure, quality of life, anxiety and depression. Implementation outcomes will be assessed using the Reach, Effectiveness, Adoption, Implementation, Maintenance (RE-AIM) framework, including a cost-effectiveness analysis. Semi-structured interviews will be conducted with participants and CVR program health professionals, investigating the acceptability, value, and impact of the CVR program. Qualitative analyses will be guided by the Consolidated Framework for Implementation Research.

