The evidence for people with TIA or stroke attending cardiac rehabilitation is limited. One large randomised controlled trial has recently been reported, the PREVENT trial, finding modest effects on vascular risk factors for stroke following a 12-week exercise and education program for people with TIA or mild stroke [30]. Two small randomised controlled trials have also been identified in the literature, although it is unclear whether these studies are stroke only cardiac rehabilitation programs or integrated programs (TIA, stroke, heart disease) [31, 32]. Additionally, the inclusion criteria differ between studies. One study included participants > 1 year post stroke and any severity [31], while the other studies included people with TIA and mild stroke within one month [32] and three months [30] of diagnosis. There is some evidence of integrated cardiac rehabilitation programs, including participants with TIA, mild stroke and coronary heart disease, using pre-post study designs [33–35]. Despite this limited evidence, all studies found that the cardiac rehabilitation model was feasible in this population, improving fitness and reducing cardiovascular disease risk [30–35]. Utilising existing cardiac rehabilitation programs for people with TIA or mild stroke may positively impact health status without creating new programs, but more robust evidence is required to determine its impact on physical function, risk factors, quality of life, morbidity and mortality, including the feasibility of conducting integrated cardiac rehabilitation programs within health services and its cost-effectiveness [26]. With no consensus on comprehensive secondary prevention programs for people post-TIA or stroke at present, and existing cardiac rehabilitation programs being a potentially suitable option, our research questions are:Is an integrated (TIA, mild stroke, heart disease) traditional exercise-based cardiac rehabilitation program effective in improving functional exercise capacity (6-min walk test distance) and quality of life, and reducing the risk of unplanned CVD-related hospital admissions, for people with TIA or mild stroke during the 6-months following commencement of the traditional cardiac rehabilitation program compared to usual care?Can an integrated traditional exercise-based cardiac rehabilitation program be implemented in existing health services, considering implementation outcome measures such as acceptability, feasibility, adoption, fidelity, and cost?

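### No deciding visit or contrast is named for 6MWT distance, and the test that reproduces the sample size of 128 is not named as primary in the analysis section

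*Protocol article*

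**What the plan says.** Outcome measures defines the primary endpoint by instrument and unit only: "The primary outcome measure will be distance completed in the 6-min walk test and reported as metres (functional exercise capacity". The same section gives the schedule: "All outcome measures will be collected at baseline, 6-weeks, and 6-months". There are therefore two post-baseline values, and neither is singled out. The research question at the end of Background refers to a period, not a visit: "during the 6-months following commencement of the traditional cardiac rehabilitation program compared to usual care".

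Data analyses puts 6MWT distance and the secondary outcomes under one approach, in which "mixed-effects models for repeated measures will be used for between-within group comparisons and time-interactions analyses", and closes with one threshold: "Significance level will be set at p < 0.05". It names no deciding comparison.

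Sample size plans one two-sided 5% test with 80% power. Its inputs are Hedges' g = 0.41, Cohen's f = 0.205, three repeated measures including baseline, and a correlation of 0.5. The result is 128 participants, raised to 140 for 8% drop-out. The section does not say which effect in the repeated-measures model is tested.

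**The concern.** A repeated-measures model of two arms at three visits gives several candidate answers: a group main effect, a group-by-time interaction, a difference at 6 weeks and a difference at 6 months. These are different quantities with different power. The stated 5% and 80% belong to one of them, and the reader cannot tell from the article whether that one will decide effectiveness.

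Two things follow. If the choice stays open until results are seen, the chance of a false positive exceeds 5%. If the sized test is the deciding one, it includes baseline, where randomisation makes the expected difference zero, so the effect being tested is diluted.

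**Working it through.** **Inputs.** From Sample size: f = 0.205, m = 3 measures, ρ = 0.5, two-sided α = 0.05, 80% power, N = 128, 8% drop-out. The article gives no SD for 6MWT, so effects are in SD units (d = 0.41). Equal variances and a common correlation across visits are assumed.

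**1. Reproducing 128 and 140** (non-central F, as in a G*Power repeated-measures ANOVA)

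- Between-groups main effect: λ = f²·N·m / (1 + (m−1)ρ) = 0.042025 × 128 × 3 / 2 = 8.07, with 1 and 126 df. Power is 80.5%, and 128 is the smallest even N that reaches 80%.
- Group-by-time interaction: λ = f²·N·m / (1−ρ), with 2 and 2(N−2) df. At N = 40, λ = 0.042025 × 40 × 3 / 0.5 = 10.09 and power is 80.3%. This test would need only 40.
- Drop-out: 64 / 0.92 = 69.6, so 70 per arm and 140 in total.

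Of these two tests, only the main effect over all three visits gives 128.

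**2. Power of that main effect when there is no difference at baseline** (normal approximation, 64 per arm)

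- Variance of a participant's three-visit mean: (1 + 2 × 0.5)/3 = 0.667, SD 0.816. Standard error of the group difference: 0.816 × √(2/64) = 0.144.
- With 0.41 SD at all three visits, baseline included: 0.41/0.144 = 2.84, power 81%. This is what the sizing assumes.
- With 0 at baseline and 0.41 SD at both follow-ups: the averaged difference is 0.41 × 2/3 = 0.273, and 0.273/0.144 = 1.89. Power is Φ(1.89 − 1.96) ≈ 47%.

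**3. Power of candidate single contrasts** (baseline-adjusted, 64 per arm, ρ = 0.5, d = 0.41)

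| Contrast | Residual variance | Power | Needed per arm for 80% |
|---|---|---|---|
| Mean of 6 weeks and 6 months | (1+0.5)/2 − 0.5² = 0.50 | 90.7% | 47 |
| One prespecified visit | 1 − 0.5² = 0.75 | 76.4% | 71 |
| Each visit at α = 0.025 | 0.75 | 66.9% | 85 |

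**4. Type I error if more than one test may decide** (simulation with no treatment effect, 64 per arm, 20,000 runs for each correlation)

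| Success if any of these has p < 0.05 | ρ = 0.5 | ρ = 0.8 |
|---|---|---|
| Change from baseline at 6 weeks or 6 months | 9.1% | 8.8% |
| Raw group difference at 6 weeks or 6 months | 8.9% | 7.4% |
| Main effect or interaction | 9.8% | 9.4% |
| Main effect, interaction or either change | 14.3% | 14.0% |

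For two tests, independence gives the ceiling 1 − 0.95² = 9.75%. Each test alone holds about 5%. Simulation error near 9% is √(0.09 × 0.91 / 20,000) ≈ 0.2 percentage points.

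**The case against.** The strongest reply is about scope. This is a condensed article, and the deciding contrast is often fixed in an analysis plan, which may exist and is not shown. An unseen plan that names one contrast would restore 5%. The article also narrows the choice: there is one primary outcome, the research question is comparative, and one two-sided test was sized. All of this stands, and it makes the error-rate statement conditional. It does not answer the mismatch inside the article, where the sized test is not named as deciding and reaches 80% only if the groups already differ at baseline.

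A reader might infer more than the text supports:

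- **That the 5% level definitely fails.** No section says that any significant result counts as success. The inflation applies only under such a rule.
- **That a gain within the CVR arm could establish effectiveness.** The comparison with usual care in Background points the other way, and the between-within wording may simply describe a mixed design. Within-arm tests do not address the treatment null, so they are not counted above.
- **That the RE-AIM phrase "change in 6-min walk distance (effectiveness" is a decision rule.** It is shorthand in a list of implementation measures and does not say that the change is uncontrolled.
- **That 14% is the size of the problem.** That figure counts overlapping tests, because the two change contrasts make up the interaction. It is an upper case.

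Averaging the two follow-ups is also one defensible choice among several. It is not the test that was sized, because it adjusts for baseline instead of pooling it.

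**Conclusion.** The point holds in a limited form. The article fixes no deciding visit or contrast for its primary outcome, and the contrast behind its sample size is absent from Data analyses as a primary test. That the sizing used a main effect is inferred from reproducing 128; Sample size does not say so.

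The firmer consequence is for power: about 47% instead of 80% for the sized main effect, assuming d = 0.41 at both follow-ups, none at baseline, and ρ = 0.5. The consequence for error is conditional: about 9%, at most 9.75%, if either follow-up may decide, and up to about 14% if the main effect and the interaction may also be used. It should be corrected before unblinding. It does not show that the trial is too small, since a well-chosen contrast is adequately powered at the planned size.

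**What to change.** In Data analyses, name one primary between-group contrast in 6MWT distance, tested at two-sided 5%. One suitable choice is the baseline-adjusted difference averaged over 6 weeks and 6 months. It fits the period in the research question and has about 90% power at 64 per arm with no added participants. One prespecified visit is also acceptable, but has about 76% power at 64 per arm. Reaching 80% would take 142 participants, and 142/0.92 = 154.3, so 155 after drop-out (156 for equal arms).

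Restate the power in Sample size for the chosen contrast. Report the other visit-specific differences as secondary estimates with 95% confidence intervals, and state that within-arm changes are descriptive.

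The cost is a few sentences and the loss of freedom to choose the better visit.
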